### Data Collection and Statistical Analysis

Data collected will be recorded on a pro-forma collection sheet and will be entered onto Microsoft Excel and the Statistical Package for the Social Sciences (SPSS v12.0). Analysis will be conducted on an intention to treat basis and withdrawals from the programme will be followed up to ensure complete data. A last measurement carried forward method will be used to predict outcome where drop-outs occur [46]. Baseline data will be reported using descriptive and frequency statistics.

Change scores occurring over the 10 week trial period and between baseline and 1 year will be compared between intervention and control groups using:

▪ Independent t tests and one-way ANOVA where data are interval or ratio level and conform to the assumptions of normality i.e. Cardiac Risk Score, VO2, Maximal work output (Watts), Peak Pressure Rate Product, Lipid profile (Total Cholesterol, HDL, LDL, Triglyceride).

▪ Non-parametric tests (Mann Whitney and Kruskall Wallis tests) will be used for ordinal level data (Hospital Anxiety and Depression Scale, Stroke Specific QoL) or where a normal data distribution is not found.

▪ Categorical variables will be analysed using Chi square tests (% smoking, % taking moderate and vigorous exercise 3 times per week, % meeting 2 fruit/3 veg daily guidelines).

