### Randomisation procedure

Since blinding to the cardiac rehabilitation programme intervention is not possible, a randomised, controlled, single-blind trial is proposed. Patients recruited for this trial will be randomly assigned to a cardiac rehabilitation group and a non-cardiac rehabilitation group. Participants will be stratified into Stroke and TIA groups and block randomisation using blocks of 12 will be performed using a computer generated randomisation schedule (SPSS v12.0) prepared by an independent party in advance. Concealed allocation will be ensured through the use of opaque sealed envelopes.

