### Exclusion Criteria

O2 dependence, angina, unstable cardiac conditions, unstable diabetes, major medical conditions, claudication, febrile illness, pregnancy or cognitive impairment.

**Sample size calculations **based on the ability to detect significant differences in the key outcome variables with 80% power and p < 0.05 are indicated in table 1. Cardiac risk data was taken from the pilot study and adherence to European guidelines for lifestyle participation in a high risk CVD group was taken from baseline data of the first 50 subjects recruited to the CRAFTS trial. The formulae for detecting change in % was n > = K [P_1_(1 - P_1_) + P_2 _(1-P_2_)]/Δ^2^. The formula for detecting a change in means was n >= 2Kσ^2^/Δ^2^K = 7.8. Our pilot study [27] resulted in a withdrawal rate of 5% overall. Based on primary outcome measures of adherence to all three European lifestyle guidelines and cardiac risk score reduction with an anticipated drop-out rate of 10%, 144 participants will be recruited. 72 randomised to the intervention group and 72 to the control group.

**Table 1 T1:** Sample size calculations

	**% adherence to European Guidelines on CVD prevention in high risk group(CRAFTS baseline data)**		**Target change to detect %**	**Sample size per group**
Moderate or vigorous exercise for 20 mins 3 or more times/week	17		Increase by 20%	73
Dietary intake of 3 vegetables portions & 2 fruit portions or more/day	21		Increase by 20%	80
No smoking % in stroke and TIA patient population	85		Increase by 15%	61
% subjects fulfilling all 3 criterion	9		Increase by 20%	56
	**Mean (sd) of baseline measures from pilot study in stroke patients**	**Mean change in intervention group – pilot study**	**Target change to detect**	
Cardiac Risk Score	9.4 (6.80)	1.52	4.0	72
VO2 exercise test	10.87 (1.71)	1.48	1.0	46
HAD – Anxiety subscale	6.13 (3.71)	0.86	1.5	54

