### Outcome Measures

The outcomes of interest can be categorised under the following headings:

1. Change in cardiovascular disease risk

2. Change in health behaviour

3. Change in body objective physical status and physical fitness indices

4. Change in self-reported functioning

The variables and measurement instruments which will be employed are summarised in table 2. Measures will be taken at baseline, at completion of the 10 week intervention programme and at 1 year post intervention. Both the short-term and long-term outcomes are illustrated.

**Table 2 T2:** Variables and measurement instruments

	Instrument	Baseline	Post Intervention	1 year Follow up

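### The between-arm tests use neither the baseline value as a covariate nor the stroke/TIA stratum; they are valid but give up precision that could be had almost free

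*Protocol article*

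**What the plan says.** The protocol article names its tests in the Data Collection and Statistical Analysis section. The stem reads "Change scores occurring over the 10 week trial period and between baseline and 1 year will be compared between intervention and control groups using", and three bullets follow:

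- For continuous outcomes: "Independent t tests and one-way ANOVA where data are interval or ratio level and conform to the assumptions of normality i.e. Cardiac Risk Score", with fitness and lipid measures also listed.
- For ordinal or non-normal outcomes: "Non-parametric tests (Mann Whitney and Kruskall Wallis tests) will be used for ordinal level data".
- For binary outcomes: "Categorical variables will be analysed using Chi square tests (% smoking, % taking moderate and vigorous exercise 3 times per week", with the fruit and vegetable guideline also listed.

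The Randomisation procedure section says: "Participants will be stratified into Stroke and TIA groups and block randomisation using blocks of 12 will be performed". The Outcome Measures section says: "Measures will be taken at baseline, at completion of the 10 week intervention programme and at 1 year post intervention". Table 2 shows a baseline reading for the cardiac risk score, exercise participation, smoking and diet.

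The article names no regression, covariance or stratified analysis. The method is therefore fixed in the text and is not a detail left open for another document.

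**The concern.** Two pieces of information are collected and then not used in the comparison of arms.

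**Baseline value.** A change score does use the baseline, but with a coefficient fixed at 1. When the true slope of follow-up on baseline is below 1, part of any chance baseline difference between the arms passes into the estimate through regression to the mean, and the variance is larger than it need be. If the chi-square tests compare percentages at follow-up, they do not use each person's starting status at all.

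**Stratum.** Stratified randomisation balances stroke and TIA across the arms. If the two diagnoses change by different amounts, a test that omits the stratum leaves that variation in its error term. Its standard error is then too large for the design.

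At stake is precision, in a trial of 72 per arm whose only observed effect on the risk score (the pilot change in Table 1) is well below the target difference.

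**Working it through.** **Inputs**

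- Cardiac risk score: baseline SD 6.80, pilot mean change in the intervention group 1.52, target 4.0, stated 72 per group (Table 1).
- Design: "with 80% power and p < 0.05 are indicated in table 1"; K = 7.8, which corresponds to a two-sided test; 72 per arm; 10% drop-out. Completers: 72 × 0.9 = 64.8, about 65 per arm.
- Baseline to follow-up correlation r: not in the document, so assumed from 0.3 to 0.9.
- Equal SD of 6.80 at both times: assumed.

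**The plan's own figure.** The stated formula gives 2 × 7.8 × 6.80² / 4.0² = 45.1, so 46 per group, not 72. That mismatch is a separate matter and does not bear on this point.

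**Variance of the two analyses**

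- Change score: 2σ²(1 − r)
- ANCOVA: σ²(1 − r²)
- Ratio, ANCOVA to change score: (1 − r²) / [2(1 − r)] = (1 + r)/2

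**Power** (noncentral t, two-sided 0.05, 65 per arm). Each power column shows the change-score t test, then ANCOVA.

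| r | SD of change | ANCOVA residual SD | Variance saved | Power for 1.52 | Power for 4.0 |
|---|---|---|---|---|---|
| 0.3 | 8.05 | 6.49 | 35% | 19%, 26% | 80%, 94% |
| 0.5 | 6.80 | 5.89 | 25% | 24%, 31% | 91%, 97% |
| 0.7 | 5.27 | 4.86 | 15% | 37%, 43% | 99%, over 99% |
| 0.8 | 4.30 | 4.08 | 10% | 52%, 56% | about 100% both |
| 0.9 | 3.04 | 2.96 | 5% | 81%, 83% | about 100% both |

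**Chance imbalance.** The standard error of the baseline difference between arms is 6.80 × √(2/65) = 1.19 points. The change-score estimate is shifted by (1 − r) times any such difference, in the opposite direction. For an imbalance of one standard error, that is 0.60 points at r = 0.5 and 0.12 points at r = 0.9.

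**Omitted stratum.** Assume two equal strata whose mean change differs by 0.5 SD. In SD units this adds 0.5²/4 = 0.0625 to the apparent variance of the change score, whose true within-stratum value is 2(1 − r). The standard error is inflated by:

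- √(1.0625/1.0) = 1.03 at r = 0.5
- √(0.6625/0.6) = 1.05 at r = 0.7
- √(0.2625/0.2) = 1.15 at r = 0.9

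A simulation of this setting (72 per arm, 2,500 runs) gave type I error of about 4%, 4% and 3% for the change-score t test at these three values, against a nominal 5%. With a 0.4 SD effect, power was 64% for the change-score t test, 76% for ANCOVA and 79% for ANCOVA plus stratum at r = 0.5. At r = 0.7 it was 85%, 90% and 92%.

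**Counts for the binary outcomes.** Table 1 gives 85% non-smoking at baseline, so 0.15 × 72 = 10.8, about 11 smokers per arm. It gives 9% meeting all three guidelines, so 0.09 × 72 = 6.5, about 6 per arm.

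**The case against.** **Validity.** A reader might infer that the planned tests are biased or that they ignore baseline altogether. Neither follows. Randomisation makes the change-score comparison unbiased on average, and a change score subtracts the baseline. Omitting the stratum errs on the conservative side, and only if the strata change differently. A stable difference in level between stroke and TIA cancels in a change score, and no figure in the document shows that the two groups change by different amounts.

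**Size.** The gain depends on r, which is unknown. The Background section says the risk score is built partly from age, sex and diabetic status, which hardly move in ten weeks, so r near 0.9 is plausible. The gain for a 1.52-point difference is then about 2 percentage points. The 1.52 is also a change within the pilot's intervention group. It is neither a between-arm difference nor the trial's target. It would be tempting to say the trial is underpowered for want of adjustment, but at its own 4.0-point target the table above does not support that. Carrying the last measurement forward would keep 72 per arm in the analysis, which raises power a little under both methods (27% to 34% at r = 0.5 for 1.52). It may also raise r and so shrink the gain.

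**Chi-square.** The change-score stem governs all three bullets, so the text does not settle whether the chi-square compares follow-up percentages or change in status. The remark about lost baseline status applies to the first reading.

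**ANOVA.** With two arms, one-way ANOVA is the t test and Kruskal-Wallis corresponds to Mann-Whitney. A reader might suspect an analysis across arm-by-diagnosis cells, but nothing in the text says so. The extra tests are redundant and harmless.

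All of these stand as limits on size and wording. They do not remove the point: with equal variances the ratio (1 + r)/2 is below 1 for every r below 1, and the stratum is known at no cost.

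**Conclusion.** The point holds as a recommendation on precision. The named tests are valid but less efficient than an analysis that uses the baseline as a covariate and the stratum. The saving in variance is 25% at r = 0.5 and falls to 5% at r = 0.9. In power, for a difference as small as 1.52 points, this is worth about 7 percentage points at the lower value and about 2 at the higher. At the planned 4.0-point difference the planned tests already reach about 80% or more for r of 0.3 or above, so adjustment is not needed to rescue the stated design.

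These figures rest on an assumed r, equal SDs at the two times, 65 analysed per arm and, for the stratum effect, an assumed 0.5 SD difference in change between stroke and TIA. No result of the trial would be invalid if the plan stayed as it is.

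**What to change.** - **Continuous outcomes:** for each outcome with a baseline reading, fit an ANCOVA of the follow-up value on arm, baseline value and stroke/TIA stratum, at ten weeks and at one year. Report the adjusted difference with its confidence interval.
- **Binary outcomes:** compare the arms with a Mantel-Haenszel analysis stratified by stroke/TIA, and state that the quantity compared is status at follow-up. Add baseline status through logistic regression, reported as a standardised risk difference, only where cell counts allow. With about 11 smokers and about 6 fully adherent participants per arm at baseline, a logistic model prescribed for every binary outcome would risk sparse cells or separation.
- **Redundant tests:** delete one-way ANOVA and Kruskal-Wallis from the two-arm comparison.

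The cost is a change to the analysis wording. It needs no new data, visits or participants. It should be made before any comparison by arm is seen.

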### Ethical Considerations and Confidentiality

The study conforms to the guidelines of University College Dublin Human Research Ethics Sub-committee (Ref HREC-19-06-[name]). Ethical approval has also been obtained from Saint James's Hospital SHJ/Adelaide, Meath and National Children's Hospitals AMNCH Research Ethics Committee (Ref REC: 2008/07/03)

All participants will be volunteers. Informed consent will be sought from participants following the distribution of an information leaflet and screening for exclusion criteria. Participants will be free to withdraw without prejudice at any time. Since the type of cardiac rehabilitation programme under investigation is not currently available to the Stroke/TIA population, there are no ethical considerations relating to the allocation of participants to a control group.

All information collected relating to participants will be confidential and will be stored securely in a locked cabinet in University College Dublin. Participants will be given a code on entering the study. This will be the only link between the participants name and data.

## Discussion

This study builds on a promising pilot study resulting in a reduced cardiac risk score and improved fitness profiles and sense of well being. It is hoped that success of the Cardiac Rehabilitation Paradigm adapted to the Stroke and TIA population will help inform the care-pathway and enhance health and social gain in this population. While a reduction of morbidity and mortality rates are not stated outcomes of this study, the incidence of new cardiovascular disease events (Cardiac death, non fatal MI, CABG, PTCA, angina, stroke death, non-fatal stroke and TIA) will be monitored in the intervention and control groups over the 1 year follow up period. It is acknowledged that the study is not powered to determine differences in morbidity and mortality, but it is planned to build on this study to determine longer term benefit.
